#### 2.5.3 Sample size

In this study, HAMD-17 is used as the leading indicator for sample size calculation. Based on the results in the preliminary clinical study, i.e., observation of the Hamilton Depression Scale score reduction (ΔHAMD) results of 6.13 ± 1.96 Mean ± SD reduction in the test group and 4.57 ± 1.87 reduction in the control group, according to the sample size calculation formula.

$$\frac{2\;(Z_{\alpha /2}+Z_{\beta }{)}^{2}\times \sigma^{2}}{\delta^{2}}$$

α = 0.05, 1-β = 0.9, σ = 1.96, δ = (6.13–4.57) = 1.56

α is set to 0.05, the statistical power is set to 0.9, and a two-sided test is conducted. Based on the calculated dropout rate of 20%, each group will eventually require 42 patients; that is, a total of 84 participants will be randomly divided into two groups in a 1:1 ratio.

### 2.6 Outcome measures

The results cover three indicators: scale indicators, serum indicators and serum metabolomics. Scale assessments will be performed at baseline, week 2 and week 4. Serum indicators and serum metabolomics will be tested at baseline and week 4. All assessments will be performed by researchers who are blinded to treatment assignment.

#### 2.6.1 The primary outcome

*2*.*6*.*1*.*1 Hamilton Depression Scale*. The Hamilton Depression Rating Scale (HAMD-17) is used to measure the severity of depressive symptoms in people with depressive disorders. The scoring content includes 17 symptom entries of depression, guilt, suicide, difficulty sleeping, lack of deep sleep, early awakening, work, interest, retardation, irritability, psychogenic anxiety, and physical anxiety, which is currently the most widely used.

In addition, the clinical effective rate is calculated by the reduced value of the HAMD-17 score (ΔHAMD), and the curative effect is judged. According to the Nimodipine method, the curative effect index was calculated according to the reduced score of the Hamilton Depression scale (HAMD-17). The formula was as follows,

$$\frac{(B-A)\times 100\%}{B}$$

A = Total score after treatment. B = Total score before treatment

The curative effect is judged as follows:

Recovery: symptom score reduction ≥ 75%.

Significantly effective: 50%≥ symptom score reduction < 75%.

Effective: 25%≥ symptom score reduction < 50%.

Invalid: symptom score reduction < 25%.

Total effective rate according to the formula

$$\frac{(R+S+E)\times 100\%}{T}$$

R = Recovery. S = Significantly effective. E = Effective. T = Total cases

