## 2 Method and analysis

### 2.1 Study design

A single-center, prospective, parallel-group, randomized controlled trial will be conducted in the First Teaching Hospital of Tianjin University of Traditional Chinese Medicine. A total of 84 PSD patients will be recruited, with those who satisfy the inclusion criteria being randomly assigned to one of two groups. One group will receive XNKQ acupuncture mainly, and escitalopram will be taken orally, and the other group will receive antidepressant acupuncture in addition to the above acupuncture treatment. All acupuncture treatments will be given six times a week for four weeks (orally take escitalopram tablets daily for 4 weeks). Outcomes include scale indicators, serum laboratory indicators, and metabolomics analysis results. The primary outcome is depressive symptom severity and corresponding changes, as assessed by the Hamilton Anxiety Scale (HAMD-17). The secondary outcomes are the severity of neurological deficit symptoms, quality of life, laboratory indicators, and serum metabolomics analysis in PSD patients. These results will be assessed by the National Institutes of Health Stroke Scale (NIHSS) and Modified Barthel Index Scale (MBI), self-rating depression scale (SDS) for self-assessment, and laboratory indicators including the determination of serum IL-1β, IL- 10 5-HT, and BDNF levels. Evaluators will conduct assessments at baseline, week 2, and week 4 (serum indicators and metabolomics analysis will be assessed at baseline and week 4). The flow chart of this trial is displayed in **Fig 1**, and the enrollment schedule is illustrated in **Table 1**.

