### 2.9 Statistical analysis

Third-party statisticians who are not engaged in the allocation process or trial implementation will be invited to conduct statistical analysis and participate in the whole process, including trial design, implementation, and data analysis. Outcome measures at baseline and two-time points after the intervention will be analyzed to assess treatment effectiveness. Data will be analyzed using SPSS26.0 software according to the intention-to-treat principle of data analysis. Subgroup analysis will be performed if data for different clinical features are available. Chi-square tests will be used to assess sample characteristics and gender. Continuous variables will be summarized as mean ± standard deviation (SD). Continuous variables will be compared by the Student t-test or Wilcoxon rank sum test, and categorical variables will be reached by the Pearson chi-square test or Wilcoxon rank sum test reported by percentage. Data conforming to the normal distribution will be analyzed by one-way analysis of variance. The comparison of each group will be analyzed by T-test. A non-parametric rank sum test and the Mann-Whitney U test will be used to assess measurement data that does not have a normal distribution or homogeneous variance. A bilateral 5% significance level will be used, and the corresponding 95% confidence interval will be calculated as far as possible. P-value <0.05 would be set as the significance level, and the difference would be considered statistically significant.

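### The protocol does not fix one primary variable and visit, and its 90% power covers only the mean HAMD-17 reduction

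*Protocol article*

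**What the plan says.** - **Abstract:** names the HAMD-17, in the singular, as the primary outcome measure. It gives no variable (score, change or responder status) and no visit.
- **Section 2.1 (Study design):** "The primary outcome is depressive symptom severity and corresponding changes". This covers both level and change.
- **Section 2.6.1 (The primary outcome):** describes the HAMD-17 and then adds: "the clinical effective rate is calculated by the reduced value of the HAMD-17 score (ΔHAMD), and the curative effect is judged". Four response classes follow, and a total effective rate that counts every patient with at least a 25% reduction. The inputs are defined as "A = Total score after treatment. B = Total score before treatment", with no week attached. Section 2.6.2, on secondary outcomes, starts only after this.
- **Section 2.6 and Table 1:** the scale is scored at baseline, week 2 and week 4.
- **Section 2.9 (Statistical analysis):** "Outcome measures at baseline and two-time points after the intervention will be analyzed to assess treatment effectiveness". One general rule follows: "P-value <0.05 would be set as the significance level, and the difference would be considered statistically significant". No order among tests or visits is given.
- **Section 2.5.3 (Sample size):** "HAMD-17 is used as the leading indicator for sample size calculation". The calculation uses mean reductions of 6.13 (SD 1.96) and 4.57 (SD 1.87). It assumes no effective rates and does not state the week of those reductions.

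**The concern.** The primary heading covers a continuous measure and a dichotomy derived from it. The score has two post-baseline visits, and nothing says which result decides the trial. The consequences are:

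1. After the data are seen, more than one result could be presented as the primary one, each judged at 5%. The chance of at least one false positive would then exceed 5%.
2. The stated 90% power belongs to the mean reduction. A reader of section 2.6.1 could assume that it also applies to the effective rate, where power is considerably lower.
3. The mean and the rate come from the same scores but can give different answers at the 5% level. The protocol has no rule for that case.

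**Working it through.** **1. The plan's own figure.** Inputs from section 2.5.3: α = 0.05 two-sided, power 0.90, σ = 1.96, δ = 1.56, dropout 20%.

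n = 2(1.960 + 1.282)² × 1.96² / 1.56² = 33.17 per group. Dividing by 0.8 gives 41.47, so 42 per group and 84 in total. The stated figure reproduces (rounding up to 34 first would give 43). With 34 completers per arm the standard error is 1.96 × √(2/34) = 0.475, and power is Φ(1.56/0.475 − 1.960) = 0.907. The calculation is sound for one comparison of mean reduction at one visit.

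**2. False-positive chance if any one result could count.** With independent tests the bounds are 1 − 0.95² = 9.75% for two and 1 − 0.95³ = 14.3% for three. These tests are correlated, so the rate was simulated under no effect. Settings: 34 per arm, 20,000 runs, reductions normal with SD 1.9, baseline uniform over 8–17 (the inclusion range in section 2.2.1), t-tests on the score, and a Pearson-type test on the 25% cut at week 4. The correlation between visits is an assumption, because the documents give none.

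| Week-2/week-4 correlation | Score at two visits | Plus week-4 effective rate |
|---|---|---|
| 0.3 | 9.1% | 12.4% |
| 0.5 | 8.7% | 12.1% |
| 0.7 | 8.1% | 11.5% |
| 0.9 | 7.0% | 10.5% |

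Repeat simulations, including runs at 42 per arm, fall within about 7–10% and 10–13%.

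**3. Power for the effective rate.** For a patient with baseline B, the cut is a reduction of 0.25B. Taking reductions as normal with the section 2.5.3 means and SDs, the rates are Φ((6.13 − 0.25B)/1.96) and Φ((4.57 − 0.25B)/1.87).

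At the mid-range B = 12.5 the cut is 3.125. The rates are Φ(1.533) = 0.937 and Φ(0.773) = 0.780, a difference of 0.157. With 34 per arm the standard error is 0.0845 under the null and 0.0823 under the alternative. Power is Φ((0.157 − 1.960 × 0.0845)/0.0823) = 0.46.

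| Common baseline HAMD | Effective rates | Power, 34 per arm | Power, 42 per arm |
|---|---|---|---|
| 8 | 98.2% vs 91.5% | 0.24 | 0.28 |
| 12.5 | 93.7% vs 78.0% | 0.46 | 0.54 |
| 17 | 83.1% vs 56.8% | 0.67 | 0.76 |

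With baselines spread uniformly over 8–17, the rates are about 92% and 76%, with power of about 0.47 at 34 per arm and 0.55 at 42. Varying the assumptions in simulation widened the range to 0.20–0.69 at 34 and 0.28–0.77 at 42. Power stays below 0.90 throughout.

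**The case against.** The strongest reply is that the document already points to one primary variable. The abstract names HAMD-17 alone, the sample size rests on the mean reduction, and section 2.6.1 introduces the effective rate as an addition, which can be read as a supportive summary of the same scale. This has weight on the variable, although the rate still stands under the primary heading with its own formula and classes. It does not settle the visit, which no section names.

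Some stronger readings are tempting, but the documents do not support them:

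- **That the trial's error rate is not 5%.** Section 2.9 gives one general level. Its sentence on two time points covers outcome measures in general, and nowhere does the protocol say that success on any one test suffices. The rates above are conditional on that inference. A test order or adjustment may also stand in an analysis plan that is not shown, so its absence is not the finding.
- **That there are four tests.** This needs a week-2 effective rate. The formula uses the score after treatment, and treatment lasts four weeks, so a single rate at week 4 is the natural reading.
- **That the effective rate is near its ceiling.** The mean control reduction of 4.57 does exceed 25% of any eligible baseline, but an implied control rate of about 76% leaves room to improve. Lower power is an ordinary cost of dichotomising.
- **That the rate has half the stated power.** That is one point in a wide range set by the assumed baseline. It also depends on whether 34 completers or all 42 randomised are analysed, and section 2.9 specifies intention to treat.

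Section 2.1 also calls the instrument an anxiety scale. The abbreviation and the rest of the article resolve this as a clerical slip, with no bearing on the point.

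**Conclusion.** The point holds in this form: the protocol does not fix one primary variable and visit, and its stated power applies only to the mean HAMD-17 reduction. The first part rests on the text alone. The sizes rest on assumptions: normal reductions, baseline within 8–17 and independent of change, and a correlation of 0.3–0.9 between visits. On these, allowing success on any result would give a false-positive chance of about 7–10% for the score at two visits and about 10–13% with the week-4 effective rate added. Power for the effective rate would be roughly 0.2–0.7 with 34 per arm and 0.3–0.8 with 42. The sample-size arithmetic is correct, and nothing here shows that the trial is too small for the mean reduction. The protocol should be changed on this point, and clarifying the text is enough.

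**What to change.** In sections 2.1, 2.6.1 and 2.9, name one primary endpoint: the between-group difference in HAMD-17 change from baseline to week 4, tested at two-sided 5%. Move the week-2 HAMD-17 and the total effective rate to the secondary outcomes, and attach week 4 to the effective-rate formula. Section 2.5.3 should confirm that the preliminary reductions were measured at the end of treatment. On that assumption 42 per group stands, with about 90% power at 34 completers per arm.

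The cost is wording only, but the sponsor gives up a primary claim on week 2 or on the effective rate. Keeping two primary tests with an equal split of the 5% would cost patients: at α = 0.025 the same formula gives 39.2, so 40 evaluable and 49–50 per group after 20% dropout. That figure covers the mean reduction only. The effective rate would need about 102 evaluable per arm for 90% power at a baseline of 12.5, even at an unsplit 5%.

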#### 2.6.2 The second outcome

*2*.*6*.*2*.*1 Self-rating Depression Scale*. Self-rating depression scale (SDS) is used to assess patients with post-stroke depression. When evaluating the curative effect, the self-evaluator should evaluate once at the baseline and once at the end of the study at two weeks and the fourth week of treatment. The SDS has 20 items, ten of which are positive and ten others negative. Before the self-evaluator evaluates, the researcher must make the subject understand the filling method of the full scale and the meaning of each question, and then make an independent self-assessment.

*2*.*6*.*2*.*2 National Institute of Health Stroke Scale*. The National Institute of Health stroke scale (NIHSS) [24] is used to evaluate the severity of neurological deficit symptoms in stroke patients. Researchers need to check and record the results quickly. Researchers cannot train or tell the patient hints unless necessary (such as repeatedly asking the patient to make a particular effort). If some items are not evaluated, they should be explained in detail in the table. Unassessed items can be reviewed and studied by monitoring video and other technical means and discussed with inspectors.

*2*.*6*.*2*.*3 Modified Barthel Index*. The modified Barthel Index (MBI) is used to evaluate the self-care ability of stroke patients; the higher the score, the stronger the patient’s self-care ability, including defecation, grooming (personal hygiene), toileting, eating, transferring, walking on level ground, dressing, going up and down stairs, and bathing. Each item has five levels and associated points. The lower the score or level of an item, the more the patient’s reliance on it.

*2*.*6*.*2*.*4 Serum laboratory index and Serum metabolomics analysis*. Serum laboratory index: determination of IL-1β, IL-10, 5-HT, and BDNF. Serum metabolomics analysis: After thawing the serum samples at room temperature, 100μL was absorbed and transferred to a fresh test tube, followed by 300μL methanol and 10μL internal standard (2- chlorophenyl alanine 2.5g/L). After the samples were mixed and centrifuged, 200μL of supernatant was sucked into the sample tube for detection by liquid chromatography-tandem mass spectrometry. The detection equipment was the AcquityTM PLC-Q-TOF-MS platform (Alfa Chemistry, USA). The advanced data features of the obtained data are extracted, processed by XCMS in R, normalized, and formed into a two-dimensional data matrix.

### 2.7 Safety evaluation and adverse events

Although acupuncture is a relatively safe treatment method with a low risk of adverse events, we require that researchers observe and ask patients about adverse reactions every time they are treated. If there is persistent soreness and difficulty in withdrawing the needle, the treatment can be stopped at any time at the patient’s discretion.

#### 2.7.1 Adverse event record

In the case report form, an "adverse event record form" is set up, requiring researchers to truthfully fill in the occurrence time, severity, duration, measures taken, and outcome of adverse events.

#### 2.7.2 Adverse event report

Severe adverse events are reported, and in that case, the researcher must take immediate measures to protect the safety of the subjects and report it to the unit in charge of the research and the ethics committee in time. The researcher should sign and date the report. The applicant will ensure that all reporting procedures required by laws and regulations are met.

### 2.8 Data collection and management

Before the start of the study, all researchers and acupuncturists will attend a three-day training course, including evaluation and collection, organized by the First Teaching Hospital of Tianjin University of Traditional Chinese Medicine. If participants can’t complete the study, these data will also be included in the statistics and kept. The case report form (CRF) will be used in this study to collect data. All personnel involved in data collection need to be confirmed and describe their work. Clinical researchers must fill in CRF accurately, timely, completely, and standardly according to the original information. The modification of CRF data must follow standard operating procedures, leaving traces of transformation. Once errors or discrepancies are found, researchers should be informed to ensure that all data records and reports are correct and complete. If necessary, the data management plan can be updated and revised in time according to the change in the research scheme, but corresponding procedures are needed to complete it. Data managers should thoroughly check the primary and secondary effectiveness indicators and key safety indicators specified in the system to ensure the correctness and integrity of these data. Any changes in the research plan will be notified to the ethics commission and the registration center promptly. This process will be carried out under the supervision of project supervision experts.

### 2.9 Statistical analysis

Third-party statisticians who are not engaged in the allocation process or trial implementation will be invited to conduct statistical analysis and participate in the whole process, including trial design, implementation, and data analysis. Outcome measures at baseline and two-time points after the intervention will be analyzed to assess treatment effectiveness. Data will be analyzed using SPSS26.0 software according to the intention-to-treat principle of data analysis. Subgroup analysis will be performed if data for different clinical features are available. Chi-square tests will be used to assess sample characteristics and gender. Continuous variables will be summarized as mean ± standard deviation (SD). Continuous variables will be compared by the Student t-test or Wilcoxon rank sum test, and categorical variables will be reached by the Pearson chi-square test or Wilcoxon rank sum test reported by percentage. Data conforming to the normal distribution will be analyzed by one-way analysis of variance. The comparison of each group will be analyzed by T-test. A non-parametric rank sum test and the Mann-Whitney U test will be used to assess measurement data that does not have a normal distribution or homogeneous variance. A bilateral 5% significance level will be used, and the corresponding 95% confidence interval will be calculated as far as possible. P-value <0.05 would be set as the significance level, and the difference would be considered statistically significant.

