## 1 Introduction

Post-stroke depression (PSD) is an affective disorder complication characterized by depression and loss of interest after a stroke, which has recently attracted more attention. According to statistics, the incidence rate of PSD in the first year of stroke is about 10% to 15%, and the incidence rate in 5 years is 39% to 52% [1]. In China, the incidence of PSD is around 34.9%, with women being more affected than men [2]. A recent animal experiment has emphasized the importance of sex specificity in determining PSD [3].

PSD manifests mainly as emotional apathy, weight change, sleep disturbance, fatigue, a sense of worthlessness, and anhedonia [4]. PSD is a negative prognosis in stroke recovery, frequently resulting in higher mortality, poorer functional recovery, significant cognitive impairment, and decreased quality of life [5].

It is essential to clarify the etiology and pathogenesis of PSD for its treatment. The occurrence of PSD is the result of a combination of social psychological factors and biological factors, including axis dysregulation, increased inflammatory factors, decreased monoamine levels, glutamate-mediated excitotoxicity, and abnormal neurotrophic responses [6, 7]. Among them, the theory of inflammatory response is one of the hotspots in the current research on the mechanism of PSD. Various inflammatory factors, primarily pro-inflammatory and anti-inflammatory cytokines that oppose each other, are implicated in the incidence of PSD, with different expressions in different phases of PSD. As antidepressant drugs can cause changes in inflammatory factors, changing the balance of inflammatory factors may be one of the strategies for treating PSD [8].

Currently, the first-line treatment for PSD is selective serotonin reuptake inhibitors (SSRIs), which can prevent and treat depression in PSD patients. However, adverse reactions such as cerebral hemorrhage, epilepsy, and gastrointestinal symptoms have increased to some extent [9]. Given the limitations of pharmacological treatment, several non-drug treatments, such as non-invasive brain stimulation, psychotherapy, exercise therapy, acupuncture, music, literature, and art, have been employed in the clinical treatment of PSD [10].

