#### 2.2.1 Inclusion criteria

Participants who meet the following criteria will be included.

Diagnosed with stroke and meet the diagnostic criteria for “Mood disorder characterized by depression or accompanied by severe depressive episode caused by a stroke can also be characterized by mania or mixed characteristics (DSM- Ⅳ)” and “Depressive disorder due to another medical condition” in the Diagnostic and Statistical Manual of Mental Disorders, Fifth Edition (DSM-V) [22].Experience a first episode of stroke onset within 6 months.Age between 35 and 80 (inclusive).The HAMD score of 8 to 17 (inclusive).Clear consciousness, stable vital signs, cooperative physical examination.

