### 2.3 Randomization

The randomization sequence will be generated by an independent statistician with the PROCPLAN procedure of the SAS9.3 statistical analysis system, which will not be involved in other trial procedures. To ensure allocation concealment, the generated random allocation sequence is placed in a sequentially coded, sealed opaque envelope, which will be opened in series, and the subjects will be assigned to either the observation or control group after the researcher determines the subject’s eligibility. To minimize bias, the allocation sequence cards in the envelope will be force-sensitive recording paper, and the researcher’s names of eligible subjects will be inscribed on the surface of the envelope before opening.

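### The stated between-arm tests use neither sex nor time since stroke, although the article itself flags sex and disease phase; the cost is precision, mainly for the serum markers, NIHSS and MBI

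*Protocol article*

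**What the plan says.** Protocol article, section 1 (Introduction): inflammatory factors are described as involved in post-stroke depression (PSD) "with different expressions in different phases of PSD". On sex, the incidence in China is given "with women being more affected than men", followed by "A recent animal experiment has emphasized the importance of sex specificity in determining PSD".

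Section 2.2.1 (Inclusion criteria): "Experience a first episode of stroke onset within 6 months". No lower limit or narrower band is given.

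Section 2.9 (Statistical analysis): "Chi-square tests will be used to assess sample characteristics and gender". Continuous outcomes are compared between arms by t-test, or by a rank test where normality or equal variance fails; one-way analysis of variance is also named. No covariate is mentioned. The only other sentence that could involve patient characteristics is "Subgroup analysis will be performed if data for different clinical features are available".

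The serum markers (IL-1β, IL-10, 5-HT and BDNF in section 2.6.2), NIHSS and MBI are secondary outcomes. HAMD-17 is primary.

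**The concern.** The article presents two patient characteristics as relevant background and then gives neither a part in estimating the treatment effect. Sex is put through a baseline significance test. Under proper randomisation that test examines a null hypothesis already known to be true, and it neither prevents nor corrects an imbalance. Time since stroke, the nearest recorded quantity to disease phase, is not used at all. A subgroup analysis does not adjust the main comparison, and here it depends on which data turn out to be available.

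If recovery or marker change over 4 weeks depends on how recent the stroke is, that variation stays in the error term. In an allocation that happens to be unbalanced, part of it moves into the estimated arm difference. This matters most for the serum markers, because the mechanistic aim rests on them and they are the outcomes for which the Introduction names phase as a source of variation.

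**Working it through.** **1. The plan's own sample size.** Inputs from section 2.5.3: α = 0.05 two-sided, power 0.90, σ = 1.96, δ = 1.56, dropout 20%.

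n per arm = 2(1.960 + 1.282)² × 1.96² / 1.56² = 33.17. Dividing by 0.8 gives 41.47, rounded up to 42. The stated 42 per arm is reproduced. The standardised effect is 1.56/1.96 = 0.796, about 0.80, and about 34 per arm are expected to be evaluable.

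**2. Chance imbalance in a binary factor, 42 per arm.** The documents give no sex ratio or distribution of time since stroke, so a prevalence of 50% is assumed. With 42 per arm, at least 10 points means a difference of at least 5 patients, and at least 20 points means at least 9.

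| Model | ≥10 points | ≥20 points |
|---|---|---|
| Hypergeometric (84 patients, 42 with the factor, 42 per arm) | 28% | 4.9% |
| Two independent binomials (42, 0.5) | 33% | 6.3% |

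**3. What a baseline chi-square test would notice.** Take a factor present in 25/42 versus 17/42, a difference of 19 points. The pooled proportion is 0.5, so every expected count is 21 and each cell deviates by 4. χ² = 4 × 4²/21 = 3.05 on 1 df, P = 0.081. The test would pass this difference. For a true 60% versus 40% difference its power with 42 per arm is about 45%. This applies to sex, which the sentence names; no test of time since stroke is stated.

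**4. Validity of the unadjusted comparison.** In 40,000 simulated trials with 42 per arm and a prognostic binary factor, the unadjusted t-test had an overall type I error of 5.1% when the factor explained 10% of outcome variance and 4.8% when it explained 30%. Among the roughly 6% of trials with an imbalance of 20 points or more, the error was about 10% and 20% respectively.

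**5. What adjustment could gain.** Let R² be the share of outcome variance explained by the covariates. The documents give no value, so a range is assumed. The residual SD is multiplied by √(1 − R²), and the standardised effect becomes 0.796/√(1 − R²). Two-sided t-test power, 34 per arm:

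| R² (assumed) | Residual SD multiplier | Effect | Power |
|---|---|---|---|
| 0 | 1.00 | 0.80 | 89.9% |
| 0.1 | 0.95 | 0.84 | 92.6% |
| 0.2 | 0.89 | 0.89 | 95.1% |
| 0.3 | 0.84 | 0.95 | 97.2% |

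Lowering the error degrees of freedom from 66 to 64 for the two covariates changes these powers by less than 0.1 percentage point. The effect used is the one planned for HAMD-17. The article gives no planning effect for the serum markers, NIHSS or MBI, so for those outcomes the residual SD column is the transferable part: confidence intervals about 5%, 11% or 16% narrower.

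**The case against.** The strongest reply is that nothing here is invalid. Unstratified 1:1 randomisation with an unadjusted t-test gives an unbiased comparison and holds its error rate overall. That stands: a reader might infer that the treatment effect is biased, and step 4 shows that it is not, except conditionally on an uncommon large imbalance.

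A second reply is that the Introduction is being stretched. It speaks of phases of the depression, not time since stroke, and of expression levels, not of change over 4 weeks. Its sex statements concern incidence and an animal experiment. It says nothing linking time since stroke to NIHSS or MBI. This also stands. Time since stroke is a proxy, and its prognostic value is an assumption, so the gain is shown as a range.

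Third, a reader might conclude that allocation is definitely unstratified and should be stratified by time since stroke. Section 2.3 describes generation and concealment and does not mention strata, but a condensed article may leave that to the full protocol. Its silence is not a finding, and the article supports no particular cut-point.

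Fourth, a reader might say that these factors receive nothing but baseline tests. Section 2.9 also foresees a subgroup analysis, however loosely, and the chi-square sentence does not name time since stroke.

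Finally, baseline P-values alter no treatment estimate, so removing them alone would gain little. What survives these replies is that section 2.9 does name its between-arm tests, and those tests are unadjusted.

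**Conclusion.** The point holds as one of efficiency, not validity. The stated comparisons leave out two baseline characteristics that should be available and that the article's own background makes plausible as sources of variation. The consequence is some loss of precision and exposure to chance imbalance, mainly in secondary outcomes.

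At the plan's own effect, the trial already sits at about its 90% target, and adjustment would take it to 93–97% if R² lies between 0.1 and 0.3. A much larger gain could be shown by assuming a smaller effect: at 0.6, power would go from 68% to 83% at R² = 0.3. The plan's effect is 0.80, so that is not the figure to rely on. If the covariates explain almost nothing, the gain is close to nil and the cost is negligible. The imbalance figures rest on the assumed 50% prevalence.

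**What to change.** In section 2.9, replace the unadjusted between-arm comparisons, at least for the serum markers, NIHSS and MBI, with a linear model containing arm, time since stroke as a continuous covariate, and sex. Fix both covariates before any unblinded look at the data, and report the adjusted arm difference with its 95% confidence interval. Replace the baseline chi-square tests with a descriptive table by arm.

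No new data should be needed. Eligibility already requires the stroke date to be known to within the 6-month window, and Table 1 lists demographic information and medical history at enrolment. The cost is two model degrees of freedom and a short amendment to the analysis text. The change leaves randomisation untouched, so it can still be made if recruitment has begun.
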